## Abstract

**Background:**

Hearing loss is the third leading global cause of disability and is associated with poorer quality of life. Hearing aids are often recommended for hearing loss; however, hearing aid uptake and use rates are perpetually low. Motivational interviewing (MI) is a patient-centered counseling aimed at addressing the desire in the patient to change their behavior. The aim of this study is to investigate the impact of one-on-one MI sessions on hearing aid use among new adult users.

**Methods:**

A multi-center, prospective, randomized patient-blind controlled trial with a pre- and post-tests design. New hearing aid users ≥ 18 years of age will be recruited from Vancouver, Canada. They will be randomly assigned to a treatment or control group. The treatment group will attend a one-on-one MI session hosted by a practicing MI therapist in addition to standard in-person audiological care. The control group will receive standard in-person audiological care. Data is collected at baseline and at 1, 3, 6, and 12 months’ follow-ups. The primary outcomes are data-logged hearing aid use hours and patient-reported outcomes as measured by the International Outcome Inventory for Hearing Aids questionnaire. Associations between intervention and hearing aid use hours and self-reported outcome measures will be assessed.

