### Outcomes {12}

#### Primary outcomes

The primary outcome is the inter-group difference in average hours of HA use at 1, 3, 6, and 12 months post-intervention aimed at assessing the early and long-term effect of the intervention. This is a quantitative measure recorded by the HAs data-logging feature.

The secondary outcomes are differences in inter-group average participant-completed questionnaire (IOI-HA) [21] scores at 1, 3, 6, and 12 months post-intervention and reported complications. The IOI-HA is an established rigorous patient reported measure for HA effectiveness [22, 23].

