### Sample size {14}

Aazh et al.’s [6] feasibility investigation of assessing HA data-logged hours of use in response to MI concluded that a standardized difference of 0.6 was best for sample size estimation. Therefore to discern this difference or greater at a 5% significance level with a power of 80%, 45 patients will be required in each intervention arm based on Machin and Campbell’s [21] clinical trial design tables. Therefore, 90 participants in total at a randomization ratio of 1:1.

An allowance of 50% participant dropout rate was adopted in this study as opposed to the 20% drop out identified by Aazh et al. to compensate for the uncertainties or anticipated higher drop rate due to the COVID-19 pandemic [6]. This higher rate is reasonable because a previous hearing aid RCT trial conducted by our senior investigators who recruited participants from audiology clinics within the greater Vancouver area, in part over the pandemic period with 3 months’ follow-up, resulted in 39.1% of participant data in the intervention arm being unavailable because of participants’ failure to attend follow-up or complete study questionnaires fully [24]. This leads to an adjusted sample size of 180 participants, 90 per group.

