**Assessments:**												
Baseline assessment												
PTA			X	X								
WRS			X	X								
Primary outcomes												
Mean hours hearing aid used					X	X	X	X	X	X	X	X
IOI-HA score					X	X	X	X	X	X	X	X

*T* Treatment group, *C* Control group, *MI* Motivational interviewing, *PTA* Pure tone audiometry, *WRS* Word recognition score, *IOI-HA* International Outcome Inventory for Hearing Aids

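### The protocol gives two different primary outcome sets and names no deciding visit, while its 80% power belongs to one single comparison

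*Protocol article*

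**What the plan says.** **Which outcome is primary.** The abstract (Methods) says "The primary outcomes are data-logged hearing aid use hours and patient-reported outcomes as measured by the International Outcome Inventory for Hearing Aids questionnaire". Table 2 places both mean hours of use and the IOI-HA score under the row heading "Primary outcomes". The Outcomes section differs: "The primary outcome is the inter-group difference in average hours of HA use at 1, 3, 6, and 12 months post-intervention", and then "The secondary outcomes are differences in inter-group average participant-completed questionnaire (IOI-HA", so the questionnaire is secondary there.

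**Which visit decides.** The Outcomes section lists four times and ranks none. It calls all four post-intervention. The Participant timeline and the data-collection section (Pre-intervention assessment at 1 month) place the MI session after the 1-month follow-up.

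**Which test.** Statistical methods {20a} names independent-samples t-tests for hours and a chi-squared test for patient-reported outcome. It does not mention visits.

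**Sample size {14}.** The cited feasibility study "concluded that a standardized difference of 0.6 was best for sample size estimation". From this, "to discern this difference or greater at a 5% significance level with a power of 80%, 45 patients will be required in each intervention arm". The total is doubled to 180 for an assumed 50% dropout.

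**The concern.** The Trial design section calls this a superiority trial. A reader should therefore be able to say in advance which single result would establish superiority, and this text does not allow that. It is unsettled whether the questionnaire counts toward the primary claim, and whether 3, 6 or 12 months, or some combination, decides.

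At stake are the error rate and the power. If the deciding result is picked once data by arm are known, 5% is not the real false-positive rate. If several results are kept and corrected for, the 80% power does not carry over, because it was calculated for one test. The second interim analysis adds urgency: at 50% follow-up it asks whether a difference in outcomes is evident and uses the answer to decide on continuation. As written, that look has no defined target.

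**Working it through.** **Inputs from the protocol:** standardized difference d = 0.6, 5% level, 80% power, 1:1 allocation, 50% dropout, visits at 1, 3, 6 and 12 months, MI after the 1-month visit. **Assumed, because the protocol gives no figure:** correlation between visits 0.5–0.85; correlation between hours and IOI-HA 0.3–0.5; IOI-HA treated as approximately normal.

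**1. The plan's own figure.** n per arm = 2(z₀.₉₇₅ + z₀.₈₀)²/d² = 2(1.960 + 0.842)²/0.36 = 43.6, so 44. The t-based solution is 44.6, so 45. A one-sided test gives 35 and does not match. Dropout: 45/(1 − 0.5) = 90 per arm, 180 in all. Power at 45 per arm: noncentrality 0.6·√(45/2) = 2.85, which gives 80.4%. The stated size is therefore correct for one two-sided comparison and contains no allowance for a second outcome or further visits.

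**2. How many visits can carry an effect.** The 1-month reading is taken before MI, so three visits per outcome remain. That makes three comparisons for hours, or six if IOI-HA is also primary.

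**3. False-positive chance if any one of these at 5% counted as success.** The independent-test ceiling is 1 − 0.95³ = 14.3% for three and 1 − 0.95⁶ = 26.5% for six. With correlated tests (simulated multivariate normal z-statistics, two-sided 5% each):

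| Visit correlation | Hours, 3 visits | Hours and IOI-HA, 6 tests (cross-outcome correlation 0.5 to 0.3) |
|---|---|---|
| 0.5 | about 12% | 22–23% |
| 0.7 | 11% | 19–20% |
| 0.85 | 9% | 16–17% |

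**4. Power if the visits were corrected instead.** Bonferroni over three visits gives 0.05/3 = 0.0167 per test. Power per test for d = 0.6 (noncentral t):

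| Evaluable per arm | One test at 5% | Each of three at 1.67% |
|---|---|---|
| 45 (50% lost, as planned) | 80% | 66% |
| 55 (39.1% lost: 90 × 0.609 = 54.8) | 88% | 76% |
| 72 (20% lost: 90 × 0.8) | 95% | 88% |

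Holding 80% per test at 1.67% needs 60 evaluable per arm, or 240 enrolled at 50% dropout.

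**5. The opposite rule.** If all three post-MI visits had to be significant, the false-positive rate would not be inflated. Power at 45 per arm would be about 63–74% (visit correlation 0.5–0.9). The 80% applies to neither rule.

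**The case against.** Several points on the other side stand.

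- **Visit-wise testing is inferred.** Statistical methods {20a} names a t-test for hours and says nothing about visits. The abstract gives the four times only as data-collection points. A reader might infer that the plan commits to four or eight separate 5% tests with any one sufficient; no passage says so.
- **A multiplicity method may exist elsewhere.** Only the protocol article is shown, and a statistical analysis plan could hold the adjustment. Its absence here is not the finding.
- **The contradiction is lopsided.** The objective, hypothesis, Outcomes section and sample size all concern hearing aid use. The Outcomes subsection headed for primary outcomes also contains the secondary ones, so the same heading in Table 2 is weak support. The abstract is the clear outlier.
- **Power depends on retention.** The drop to 66% occurs only if the full 50% is lost. With 20% lost, even the corrected test exceeds 80%. On the other hand, the 39.1% figure comes from one arm of a 3-month study, and 12-month loss could be higher.
- **The questionnaire may not be tested as modelled.** The plan assigns chi-squared to patient-reported outcome, so the six-test figures are illustrative.

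These points narrow the finding but do not remove it. The two primary sets both stand in the current text, and the Outcomes section itself defines the primary outcome at several times without a deciding one.

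**Conclusion.** The point holds as an internal contradiction on the primary outcome, together with a primary outcome that has no deciding comparison. Under an any-visit rule the false-positive chance would be about 9–12% for hours, or about 16–23% with IOI-HA included. Both ranges rest on that hypothetical rule and on the assumed correlations. Bonferroni over three visits would leave about 66% power at 45 evaluable per arm and 76% at 55.

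Two stronger readings are not supported. The sample size is not miscalculated: it is right for one comparison, and the fault is that the protocol does not say which. Nor can it be said that the trial will run at an inflated error rate, since no success rule is stated and an analysis plan may exist. Counting four visits per outcome would also overstate the size, because the first reading precedes MI.

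**What to change.** 1. Name data-logged hours as the only primary outcome in the abstract, the Outcomes section and Table 2, with IOI-HA secondary in all three.
2. Remove the 1-month pre-MI reading from the primary comparison, and correct the wording that calls it post-intervention.
3. Before outcome data are seen by arm, and so before the second interim analysis, designate one deciding comparison at two-sided 5%. It can be a single overall contrast across 3, 6 and 12 months, or one named post-MI visit with the other visits tested after it in a fixed order.
4. State in Sample size {14} that the 80% power refers to that comparison.

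**Cost.** A formal amendment with ethics approval, as the protocol requires for such changes, in a trial that began recruiting in March 2021. No extra patients: with one named visit deciding, 45 evaluable and 90 enrolled per arm stand. For an overall contrast, the 0.6 would have to be stated on that contrast's own scale.

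**Trade-off.** Under a fixed order the later claim depends on the first. At 45 per arm, power to pass both of two steps is about 70–75% (d = 0.6 at each, visit correlation 0.5–0.85, normal approximation). This matters because the objective covers both short and long term. The single contrast avoids the dependence but gives no separate long-term claim. The choice is the sponsor's; what matters is that it is fixed in advance.

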**Discussion:**

This trial is designed to evaluate the efficacy of one-on-one MI in improving hearing aid use in new adult users in the short and long terms. Results will contribute to the evidence on whether MI counseling has an effect on hearing aid use and may guide future clinical practices.

**Trial registration:**

ClinicalTrials.gov NCT04673565. Registered on 17 December 2020.

**Supplementary Information:**

The online version contains supplementary material available at 10.1186/s13063-023-07352-7.

## Administrative information

Note: the numbers in curly brackets in this protocol refer to SPIRIT checklist item numbers. The order of the items has been modified to group similar items (see http://www.equator-network.org/reporting-guidelines/spirit-2013-statement-defining-standard-protocol-items-for-clinical-trials/).

## Introduction

### Background and rationale {6a}

#### Hearing loss

Sensorineural hearing loss can be defined as reduced hearing ability secondary to dysfunction of the inner ear or auditory nerve. Presbycusis, or age-related hearing loss, is the most common form of sensorineural hearing impairment.

Hearing impairment is associated with anxiety, depression, safety concerns, lack of mobility, and reduced employment opportunities and income [1]. The 2019 Global Burden of Disease Report estimates that 1.57 billion people worldwide suffer from hearing loss and that hearing loss is the third leading cause of human disability [2].

#### Hearing aids

Many studies demonstrate that hearing aid (HA) use increases the user’s ability to detect, differentiate, and locate sound and improve speech recognition and health-related quality of life (HRQoL). A review by Chisolm et al. [3] assessed the effect of amplification on HRQoL and concluded that HAs had a medium-to-large effect. Other reviews on the effects of HAs on quality of life have reached similar conclusions [4, 5].

Despite these findings, HA uptake and use are generally poor. A UK National Health Service survey indicated that approximately 40% of new patients use their HAs for less than 4 h a day [6]. Similar conclusions have been reported in other comparable countries [7, 8]. Reasons for this lack of use include disappointment with HA effectiveness, perceived lack of need for a HA, affordability or cost concerns, and the social stigma [9–11].

#### Person-centered counseling

Person-centered counseling has been popularized in audiology literature in the past decade. Person-centered counseling, initially developed by Carl Rogers, facilitates the discovery of the client’s own intrinsic tendency toward healing and growth [12]. Laplante-Lévesque et al. found that the therapeutic relationship between the audiologist and the patient is an important determinant of HA use [12, 13]. Motivational interviewing is one potential intervention that may be utilized to increase HA use.

#### Motivational interviewing

Motivational interviewing (MI) is a patient-centered counseling technique that describes readiness to change as a dynamic rather than a static state [14]. MI is aimed at eliciting behavioral change by exploring and resolving a patient’s ambivalence. MI has been successfully used to increase adherence to long-term treatment and promote behavioral change in other medical fields [15–17].

Several studies have investigated the impact of MI on HA use [6, 18, 19]. However, these studies have had significant limitations. Aazh et al. [6] and Ferguson et al. [19] studies were only pilot studies and had limited power, while Solheim et al. [18] did not use a control group. Furthermore, none of the above studies considered the long-term outcomes of MI and whether these positive results would persist. A recent systematic review found no robust evidence that MI significantly improved HA use or user-reported outcomes, and concluded that future research is warranted [20].

#### Justification

Hearing loss is the third leading cause of disability globally and HA use can improve a client’s hearing ability and quality of life. MI is a technique shown to be effective in addressing other chronic conditions and so far, definitive evidence of its efficacy or otherwise in the hearing-impaired population is lacking. The investigative team of this study includes an experienced clinical trialist, otolaryngologist, motivational therapist, and dispensing audiologists. These experts designed a randomized controlled trial study protocol to determine the efficacy of the intervention, one-on-one MI, in improving adherence to HA use in new clients in the short and long terms.

### Objectives {7}

The primary objective is to determine the efficacy of one-on-one MI in increasing adherence to HA use in new adult clients in the short and long terms. The secondary objective is to determine if there are adverse effects associated with one-on-one MI.

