### Methods in analysis to handle protocol non-adherence and any statistical methods to handle missing data {20c}

Sample population to be analyzed will be based on randomization. Any participant’s missing age data will be imputed with the mean of age of their allocation group. Missing sex data will not be analyzed. Participants without or with incomplete main outcome data including data-logged HA use hours and IOI-HA scores will be excluded from analysis.

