### Adverse event reporting and harms {22}

After participants have provided consent and enrolled in the study, adverse events will be collected and recorded until the end of the study period. Adverse events that occur after consent is signed, but before receiving the study intervention will be reported as not related to our intervention. Any serious adverse event that occurs will be reported to the institutional review board (IRB) and will be documented.

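### The exclusion for incomplete hours or IOI-HA is not limited to those outcomes and conflicts with the retention rule, so the population for the harms objective is ambiguous and could shrink to completers

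*Protocol article*

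**What the plan says.** - **Objective.** Objectives {7} gives the trial one secondary aim, worded as: "determine if there are adverse effects associated with one-on-one MI".
- **Outcome.** Outcomes {12} lists as secondary outcomes the IOI-HA "scores at 1, 3, 6, and 12 months post-intervention and reported complications".
- **Collection.** On harms, section {22} of the article reads: "After participants have provided consent and enrolled in the study, adverse events will be collected and recorded until the end of the study period". Section {11b} also records accidental injuries and withdrawals of consent.
- **Exclusion rule.** The section on non-adherence and missing data {20c}: "Participants without or with incomplete main outcome data including data-logged HA use hours and IOI-HA scores will be excluded from analysis". The same section opens by basing the analysed population on randomisation.
- **Retention rule.** The section on retention and complete follow-up {18b} says that when a participant withdraws early, whatever was gathered before then is kept and used in the analyses.
- **Expected loss.** Sample size {14}: "An allowance of 50% participant dropout rate was adopted in this study". The section also cites 20% from a feasibility study, and 39.1% unavailable data in the intervention arm of an earlier trial from the same region with 3 months' follow-up.
- **Timing.** Participant timeline {13} and the outcome assessment section {18a} place the MI session after the 1-month visit.

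**The concern.** The {20c} exclusion removes people, not data items. The sentence just before it, on missing sex, drops only an item. Nothing in the exclusion confines it to analyses of hours or IOI-HA, so on its wording it also reaches complications, which are a stated secondary outcome.

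The rule also falls on the participants who matter most for harms. Because MI follows the 1-month visit, someone who leaves because of the session has at most 1-month data and lacks the 3-, 6- and 12-month hours and IOI-HA. That record is incomplete, and only the MI arm can lose people for this reason. If leaving is related to a bad reaction, a comparison among completers would lean towards finding no adverse effects. Events already collected on the others would go unused.

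**Working it through.** **1. The plan's own figure.** With a standardised difference of 0.6, two-sided 5% and 80% power, the t-test solution is 44.6, so 45 per arm (power 80.4% at 45). The article does not state sidedness; two-sided reproduces its figure. Inflation for 50% loss gives 90 / (1 − 0.5) = 180 in total, 90 per arm. Both figures reproduce.

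**2. The two rules for one participant.** Take someone randomised to MI who attends the session, reports a complication and withdraws before month 3.
- Under {22}, the event is recorded.
- Under {18b}, the data up to withdrawal are kept and analysed.
- Under {20c} as worded, hours and IOI-HA are incomplete and the participant is excluded from analysis.

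The last two give opposite answers, and the article does not say which governs harms.

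**3. Size of a completer set.** Completers per arm = 90 × (1 − d). With no events among n participants, the one-sided 95% upper bound on the rate is 1 − 0.05^(1/n).

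| Loss d | Source | Completers per arm | Zero-event upper bound |
|---|---|---|---|
| 50% | planning allowance | 90 × 0.50 = 45 | 1 − 0.05^(1/45) = 6.4% |
| 39.1% | earlier trial, intervention arm | 90 × 0.609 = 54.8, about 55 | 1 − 0.05^(1/55) = 5.3% |
| 20% | feasibility study | 90 × 0.80 = 72 | 1 − 0.05^(1/72) = 4.1% |
| none excluded | all randomised | 90 | 1 − 0.05^(1/90) = 3.3% |

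**4. Chance of seeing at least one event.** This is 1 − (1 − p)^n. For an assumed true rate of 2% it is 60% with 45 and 84% with 90. For an assumed 3% it is 1 − 0.97^45 = 74.6% and 1 − 0.97^90 = 93.6%.

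The figures for 90 in steps 3 and 4 are a ceiling. They treat all 90 as exposed to MI and fully observed. Under the same loss, some leave before MI and others are observed for less time.

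**5. Selective loss (assumed figures).** Suppose 10% of the 90 MI participants (9 people) have a reaction and 45 of the 90 complete. If a fraction q of the 9 leave, the rate among completers is 9 × (1 − q) / 45:
- q = 50%: 4.5 / 45 = 10%, no bias
- q = 75%: 2.25 / 45 = 5%
- q = 100%: 0 / 45 = 0%

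The bias depends wholly on whether leaving is related to the reaction. The article has no data on that.

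**The case against.** The strongest reply is that the exclusion is triggered by missing main outcome data, namely hours and IOI-HA, and is most naturally read as governing the analyses of those outcomes. The statistical methods section {20a} lists no harms comparison for it to shrink, {20c} itself starts from the randomised population, and {18b} keeps withdrawn participants' data. A named safety set, rate definitions and interval methods usually sit in a SAP or full protocol, neither of which is shown.

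Much of this stands. A reader might infer that harms will be judged on about 90 completers in total and that people who leave after a reaction disappear from the comparison. The article does not support that: it never applies the exclusion to harms, {18b} points the other way, and 45 per arm is an allowance, not a forecast. The absence of a detailed harms analysis is not a fault here either.

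Three further replies have weight:
- **The alternative is not 90 fully observed people**, as noted in the working.
- **All randomised participants is not the only defensible set.** It puts people who never attended MI in the MI denominator, and a set of MI recipients could also be justified.
- **Harms is one consequence of a wider conflict** between {18b} and {20c} that also touches the primary outcome. But settling that conflict for hours alone, for example by keeping a complete-case analysis there, would leave harms open unless the exclusion's scope is stated.

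What the objection does not remove is that two current rules disagree about the same participant, and that the exclusion is written without a limit. That is a contradiction in stated text, not detail left for later.

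**Conclusion.** The concern holds as an ambiguity with a harmful literal reading. {20c} and {18b} contradict each other for withdrawn participants, and the wording of {20c} permits the harms objective to be answered from completers although events are collected on all enrolled.

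On that reading the harms set falls from 90 to about 45, 55 or 72 per arm at the three loss rates the article quotes. At the planned loss, the rate that zero events can exclude moves from at best 3.3% to 6.4%. A bias towards no harm follows only if leaving is related to a reaction, which is plausible but not shown. The article expects low risk in both arms ({11b}), so the matter is worth correcting but does not threaten the trial.

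**What to change.** - Limit the {20c} exclusion to the analyses of data-logged hours and IOI-HA.
- Reconcile {20c} with {18b}, so that one rule says what happens to data collected before withdrawal.
- State that adverse events and complications are reported by randomised arm for all randomised participants, using all data up to withdrawal, and show alongside how many in the MI arm actually received the session.

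The form of the rates and intervals can be left to the SAP.

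The cost is two or three sentences, with no new data or participants. The downside is that those who drop out contribute shorter follow-up, and non-attenders slightly dilute the rate in the MI arm. Showing the number who received MI makes that dilution visible.
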